## 4.4 Safety analysis

All safety analyses were based on SS unless otherwise specified.

### 4.4.1 Drug Exposure and Compliance Analysis

Days on medication and total doses taken during the treatment period will be summarized by treatment groups, and the number of non-missing data, mean, standard deviation, median, minimum, and maximum will be calculated.

Medication compliance was calculated according to the following rules:

$$\text{Medication compliance} = (\text{actual dose/planned dose}) * 100\%$$

Frequency and percentage of medication compliance will be calculated as < 80%, 80% to 100%, and > 100% in addition to the number, mean, standard deviation, median, minimum, and maximum calculated for medication compliance by continuous variables.

Summaries of drug exposure will also be summarized separately by age ( $\leq 65$ ,  $> 65$ ) and renal function class (normal, mildly impaired, and moderately to severely impaired).

Subjects will also be listed for study drug intake during the trial.

### 4.4.2 Adverse Events

Adverse event data will be coded according to the current version of MedDRA. Treatment Emergent Adverse Event (TEAE) will be used in the analysis, while adverse events that start prior to the first dose of study medication (pre-treatment) will not be involved into the safety

analysis. Adverse events on study medication (during treatment) and after the last dose of study medication (post-treatment) will be analyzed.

The differences in the proportions of patients with AE between treatment groups and their corresponding 95% CIs will be estimated based on Newcombe–Wilson. The ORs and 95% CIs will be estimated with the logistic regression. Chi-squared test or Fisher’s Exact test will be used to compare the number of each AE combination according to system organ class and preferred term between treatment groups.

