In the more than 2 years since the launch of edaravone in Japan, the number of patients treated with edaravone in Japan was about 310,000, and 162 cases of acute renal insufficiency (0.052% of users) were reported, including cases with unknown causality. The occurrence time of adverse reactions showed that 155 of 162 cases had clear occurrence time, of which 85 cases occurred within 7 days after administration and reached the peak 4 days after administration. Hishida reported that among 207 patients with renal dysfunction during the administration of edaravone, 8.2% of the cases with renal insufficiency was highly related to the administration of edaravone and 34.8% of that was possibly related.

A monitoring study of adverse reactions conducted by the regulatory authority of Mitsubishi Pharmaceutical found that the incidence of edaravone related liver dysfunction was 4.3% and edaravone was considered a possible cause of renal dysfunction. Fulminant hepatitis was a serious drug-related adverse reaction of edaravone recently observed. According to statistics, 7 cases of fulminant hepatitis reported in Japan from April 2003 to February 2007 were related to the clinical application of edaravone.

According to all serious adverse reactions reported, although some serious adverse reactions are extremely rare, edaravone still adds new safety warnings, including granulocytopenia, acute lung disease, rhabdomyolysis, and hepatitis. In the revision of the 14th edition in 2009, the instructions for edaravone injection in Japan listed 7 serious adverse reactions: 1. acute renal failure, nephrotic syndrome; 2. fulminant hepatitis, liver failure,

jaundice; 3. thrombocytopenia, granulocytopenia; 4. diffuse intravascular coagulation (DIC); 5. acute lung injury; 6. rhabdomyolysis; 7. shock. allergic reactions.

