**2.3. Main estimated target**

The main clinical concerns of this study: Based on treatment policy strategy, the efficacy of Y-2 Sublingual Tablets versus placebo in patients with acute ischemic stroke was assessed by the proportion of participants with an mRS score  $\leq 1$  at Day 90 after treatment, regardless of whether the participants had delayed or discontinued the administration, or used protocol-allowed concomitant medications (as specified in Section 5.8.1) due to adverse events.

The main estimated target consists of the following attributes:

- Population: adult patients with acute ischemic stroke. The study population in this trial is determined by the inclusion and exclusion criteria defined in Section 4;
- Treatment: Y-2 Sublingual Tablets 36 mg (containing 30 mg of edaravone and 6 mg of dexborneol) or Y-2 placebo control (containing 60  $\mu$ g of dexborneol to simulate the cool taste of sublingual administration of the investigational product) BID for 14 consecutive days, 28 times in total;
- Endpoint: treatment compliance status derived from the mRS score at Day 90 after treatment (compliance: mRS score  $\leq 1$ );
- Handling of other concomitant events:
  - Use of concomitant medications/therapies during the treatment period but continued with investigational product treatment and follow-up after

investigator assessment; or delay, interruption of administration, or discontinuation of the treatment due to AEs, but no early withdrawal from the study; or mRS scores at required time points could only be obtained through remote visit due to the impact of COVID-19: Use of treatment policy strategy (regardless of the occurrence of such events);

- No mRS score after initiation of the treatment for any reason; or early discontinuation of treatment or withdrawal from the study due to death; or early withdrawal from protocol-specified follow-up due to AEs: use of a composite strategy (occurrence of such events was counted as a substandard mRS score);
- Early discontinuation of the treatment or withdrawal from the study for reasons other than those mentioned above: use of the while-on-treatment strategy (i.e., mRS compliance status was evaluated based on the mRS score closest to the withdrawal from the study).

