### **5.5. Treatment protocol**

Take 1 tablet of the drug sublingually each time. Place the drug at the edge of the lingual frenulum, and keep it until there is no obvious foreign body sensation. Avoid chewing or swallowing undisintegrated drugs directly during administration.

The first dose should be administered as soon as possible after randomization; According to the results of human pharmacokinetic study, the plasma concentration has decreased to 1/10 of Cmax 6 hours after administration. The second dose should be not less than 6 hours but not more than 12±1 hours from the first dose. The drug should not be administered more than 2 times a natural day; Each subsequent dose should be taken for 14 consecutive days (28 doses) at an interval of 12 ± 1 h (calculated with the fixed administration time as the baseline point).

Each subject should only take up to 28 doses. If the medication is missed or suspended halfway, the subject should continue to take the drug after 14 days, but not more than 28 doses or 14+3 days. Backup drugs should only be used in the following cases, otherwise they should be uniformly recovered to the Sponsor.

- 1) Loss of drugs;
- 2) Breakage of drugs.

If all 30 tablets are taken, it is inferred from the available toxicological evidence that there will be no significant risks in theory, but such incidents still need to be truthfully recorded.

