[5] mRS score before this onset.

[6] Completion after SSS TOAST classification and enrolling is acceptable.

[7] Use as soon as possible after randomization.

[8] Concomitant medications and adverse events should be recorded from the time of signing the informed consent form to Day 90 of medication or the last follow-up.

If adverse event occurs, the subject will be followed up until the adverse event disappears or is restored to baseline levels or is not clinically significant.

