## **8.5. Safety analysis**

Data for safety evaluation include adverse events observed during the study and changes in laboratory data before and after treatment. Adverse event data are processed in statistical analysis after encoding according to the current version of MedDRA at the time of encoding.

Adverse events, adverse events during the study period since the first dose of the drug, major adverse events, unexpected adverse events, adverse event of special interest, serious adverse events, adverse events related to study drugs and serious adverse events related to study drugs are classified by system organ class and preferred term. Among them, significant adverse events are defined as adverse events that require drug therapy or non-drug therapy for the subject reporting the event; adverse events of special interest are divided into three types, i.e., liver function impairment, renal function impairment and hypokalemia. The Sponsor's clinical research associate is responsible for confirming and classifying all adverse events before unblinding.

If multiple adverse events occur in the same subject, the incidence rate is counted as 1 case; When the same AE occurs multiple times, the incidence of this AE is counted as 1. Adverse events will be summarized in frequency tables according to the system organ class (SOC) and preferred term (PT). The incidence is calculated by system, symptom/sign (count of cases: number of subjects who have experienced at least one adverse event).

The list of subjects experiencing adverse events and the list of subjects experiencing SAEs are provided. With respect to the laboratory data, in addition to the mean comparison before and after treatment, details of cases that are normal before treatment and abnormal after treatment or cases with abnormalities before treatment and abnormality exacerbation after treatment are mainly analyzed and listed. Refer to the statistical analysis plan for other details.

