### 2.3 Study Endpoints

- **Primary Efficacy Endpoint**
  - The proportion of patients with mRS score  $\leq 1$  on Day 90 after randomization.
- **Secondary Efficacy Endpoints**

- mRS score on Day 90 of treatment;
  - the proportion of patients achieving a good functional outcome (mRS  $\leq 2$ ) on day 90;
  - the change in NIHSS score from baseline to 14 days.
  - the proportion of patients achieving an NIHSS score  $\leq 1$  on day 14, 30 and 90 days after randomization.
- **Safety Endpoints**

Safety evaluation include:

- adverse events within day 90.
- treatment related adverse events within day 90.
- changes in vital signs and laboratory data before and after treatment.

According to the protocol, exploratory biomarker studies will also be conducted in parallel in this study, and data collection and analysis will be handled separately and not included in this statistical analysis plan.

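### As naturally read, the adverse-event comparisons pool first dose to Day 90 although dosing lasts 14 to 17 days; adding a descriptive on-treatment comparison is a cheap improvement

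*Combined protocol and SAP*

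**What the plan says.** **Window.** SAP 2.3 lists as a safety endpoint "adverse events within day 90", and treatment-related events over the same span. Collection matches this: the flow-chart notes in Protocol 6 have events recorded from consent until Day 90 or the end of follow-up. SAP 4.4.2 sets the start of the analysis window by ruling that "adverse events that start prior to the first dose of study medication (pre-treatment) will not be involved into the safety" analysis, then adds: "Adverse events on study medication (during treatment) and after the last dose of study medication (post-treatment) will be analyzed".

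**Tests.** SAP 4.4.2 then specifies a difference in the proportion of patients with an adverse event (Newcombe–Wilson interval), an odds ratio from logistic regression, and chi-square or Fisher tests by system organ class and preferred term. SAP 4.4.3 repeats this for serious events. Neither section attaches a period to any test. Protocol 8.5 lists, among other classes, "adverse events during the study period since the first dose of the drug", serious events, related events and three types of special interest (liver, renal, hypokalemia). It has no on-treatment class, and a patient with several events counts once.

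**Exposure.** Protocol 2.3 gives the regimen as "BID for 14 consecutive days, 28 times in total". Protocol 5.5 lets missed doses be made up, "but not more than 28 doses or 14+3 days". After the last one-tablet dose, mean half-lives are 3.76 h for edaravone (Table 1.2-6) and 4.02 h for dexborneol (Table 1.2-7).

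**Terminology.** Protocol 2.2.3 uses TEAE for treatment-related events, while the SAP abbreviation list expands it as treatment-emergent. Neither gives an end to the window.

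**The concern.** A short course followed by a long observation period makes a cumulative, one-count-per-patient comparison insensitive to harm during exposure. A patient with an on-drug event and a later complication counts the same as one with only the later complication. If later events are about equally common in both arms, they add to both proportions, shrink the difference and widen its standard error.

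Safety is half of the stated objective. The risk section (Protocol 1.3) gives one reason to look early. Of the post-marketing acute renal insufficiency cases on edaravone, 155 had a known onset time, "of which 85 cases occurred within 7 days after administration and reached the peak 4 days after administration". Renal impairment is also one of the three events of special interest. A Day 90 table showing little difference could then be taken as reassurance about the dosing period, which it was not built to give.

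**Working it through.** **1. The plan's own figure.** With 50% v 40%, two-sided 0.05, 80% power and 1:1 allocation (SAP 2.5):

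n = [1.960·√(2 × 0.45 × 0.55) + 0.842·√(0.25 + 0.24)]² / 0.10² = 387.3, so 388 per arm; 388 / 0.85 = 456.5, so 457.

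This reproduces the plan's 388 and 457. It is an efficacy calculation. The documents state no adverse-event rate, detectable safety difference or safety power.

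**2. Off-drug share of the window.** (90 − 14)/90 = 84%; at the longest dosing period, (90 − 17)/90 = 81%. Five mean half-lives after the last one-tablet dose are 5 × 3.76 = 18.8 h and 5 × 4.02 = 20.1 h. With the longest mean half-life reported (7.90 h, dexborneol, two tablets) the figure is 39.5 h.

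**3. Dilution.** Let c and t be the on-treatment risks (control, drug) and q the post-treatment risk, equal in both arms and independent of on-treatment events. The risks by Day 90 are 1 − (1 − c)(1 − q) and 1 − (1 − t)(1 − q), so

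pooled risk difference = (t − c)(1 − q).

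Worked case: c = 0.20, t = 0.28, q = 0.20. Control: 1 − 0.80 × 0.80 = 0.360. Drug: 1 − 0.72 × 0.80 = 0.424. Difference: 0.064 = 0.08 × 0.80.

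**4. Illustrative size.** Power = Φ[(d − 1.96·SE₀)/SE₁], with d the difference and SE₀ and SE₁ its pooled and unpooled standard errors, 457 per arm, two-sided 0.05. All values of c, t and q are assumptions; q = 0 is the on-treatment comparison.

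| On treatment, control v drug | q | By Day 90 | Difference (points) | OR | Power |
|---|---|---|---|---|---|
| 5% v 10% | 0 | 5.0% v 10.0% | 5.0 | 2.11 | 82% |
| | 20% | 24.0% v 28.0% | 4.0 | 1.23 | 28% |
| | 50% | 52.5% v 55.0% | 2.5 | 1.11 | 11% |
| 20% v 28% | 0 | 20.0% v 28.0% | 8.0 | 1.56 | 81% |
| | 20% | 36.0% v 42.4% | 6.4 | 1.31 | 51% |
| | 50% | 60.0% v 64.0% | 4.0 | 1.19 | 24% |
| 30% v 39% | 0 | 30.0% v 39.0% | 9.0 | 1.49 | 82% |
| | 20% | 44.0% v 51.2% | 7.2 | 1.34 | 59% |
| | 50% | 65.0% v 69.5% | 4.5 | 1.23 | 30% |
| 2% v 5% (rarer event) | 0 | 2.0% v 5.0% | 3.0 | 2.58 | 69% |
| | 4% | 5.9% v 8.8% | 2.9 | 1.53 | 38% |
| | 8% | 9.8% v 12.6% | 2.8 | 1.32 | 26% |

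In the rarer-event rows the risk difference hardly moves. The loss there is mainly of precision, and of contrast on the odds-ratio scale.

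**5. Timing of the renal cases.** 85/155 = 55% within 7 days; the other 70/155 = 45% are not placed in that week.

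**The case against.** **Pooling is not stated.** The key sentence labels two periods and says neither that they are combined nor that they are kept apart. That is correct, and a reader should not take pooling as established. It remains the natural reading, given a Day 90 endpoint and one untimed proportion per arm. If separate comparisons were meant, the SAP gives no boundary between the periods, so it needs a sentence either way.

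**Safeguards exist.** Related events are a separate endpoint with their own between-arm comparison (Protocol 8.4), and the causality assessment weighs the interval from first and last dose (Protocol 7.3.5). Tests by system organ class and preferred term face a lower background than any-event tests. Vital signs are compared to Day 14 (SAP 4.4.4), and laboratory tests are taken at Day 7 and Day 14. So a reader should not infer that every safety comparison is diluted. None of these, however, is a randomized comparison of all adverse events within the exposure window, because relatedness rests on case-by-case judgement.

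**Tempting stronger readings.** A reader might infer from Protocol 1.3 that the main edaravone harm falls in the first week. The text covers only post-marketing renal cases, 45% of the dated ones are outside that week, and liver dysfunction, the most frequent reaction in the Japanese pre-approval trials, is given no onset time. A reader might also suppose that most patients have some event by Day 90. The documents give no such rate, and Protocol 7.3.1 excludes expected progression of the stroke, which lowers the background.

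**The Day 90 risk is a legitimate endpoint.** It captures delayed harm, and half-life does not bound how long an effect lasts. In the dogs given the intravenous product, ALT, AST and bilirubin stayed relatively high and recovered after 2 weeks (Table 1.2-3). This stands. It argues for keeping the Day 90 comparison, and against a lag set by half-life alone. Visit 3 falls on Day 14 (+3), or Day 15 + 3 when the last dose is on Day 15, so a 2-day lag could place an end-of-treatment laboratory abnormality in the off-drug period.

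**No safety power is claimed.** The SAP's significance level is set for efficacy analyses. Power serves here only as a yardstick for lost sensitivity.

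**Conclusion.** The point holds as a cheap improvement, not as an error in the declared endpoint. Dosing lasts 14 to 17 days, the endpoints run to Day 90, and no on-treatment boundary or between-arm adverse-event comparison by period is specified. On the natural reading, 81% to 84% of the compared window is off drug.

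The direction of the dilution follows from q > 0 and equal in both arms, independent of on-treatment events, with 457 per arm close to the safety set. The factor is (1 − q) on the risk difference. In the first three scenarios of the table, q of 20% to 50% takes power from 81–82% down to between 11% and 59%. These figures are illustrative because the documents give no adverse-event rates for this trial. If the drug also caused late events, q would differ between arms and the Day 90 comparison would pick up what an on-treatment one misses. The two belong side by side.

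**What to change.** Keep the comparison from first dose to Day 90 as the declared endpoint. In SAP 4.4.2 and 4.4.3 add the same between-arm comparisons, labelled descriptive, for any adverse event, serious events, related events and the three events of special interest in Protocol 8.5. Assign each event by onset date to:

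- (a) first dose to last dose + 3 days, extended to include abnormalities first found in the Visit 3 samples;
- (b) after (a) to Day 90.

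State whether the Visit 3 extension also applies to patients who stopped dosing early. Give TEAE one meaning in the protocol and the SAP, with an end to its window.

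**Cost.** SAP wording and two more columns per table. Onset dates are collected and have imputation rules (SAP 4.1.3), and days on medication are already summarized (SAP 4.4.1). No patients, visits or data are added. The downside is more safety comparisons to read, hence the descriptive label.

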#### **4.4.3 Severe Adverse Events**

The differences in the proportions of patients with SAE between treatment groups and their corresponding 95% CIs will be estimated based on Newcombe–Wilson. The ORs and 95% CIs will be estimated with the logistic regression. Chi-squared test or Fisher’s Exact test will be used to compare the number of each SAE combination according to system organ class and preferred term between treatment groups.

#### **4.4.4 Vital Signs and Laboratory Test Examination**

Within each treatment group, the number and percentage of subjects with elevated in vital signs from baseline to day 14 after randomization will be described and Fisher’s Exact test will be used to compare the difference between treatment groups. The baseline measurements and changes after treatment of blood routine and bloodbiochemistry will be described as "abnormal and clinically significant" will be determined by the researchers. Within each treatment group, the number and percentage of subjects with an "abnormal and clinically significant" value will be summarized and Fisher’s Exact test will be used to compare the difference between treatment groups.

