**2.2.3. Safety outcomes**

- Incidence of adverse events (AEs) in each group;
- Incidence of treatment-related adverse events (TEAEs) in each group;
- Changes in vital signs and laboratory data in each group before and after treatment.

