**6.3. Follow-up period****6.3.1. D30 ( $\pm 7$ ) (visit 4)**

- Vital signs and physical examination (including weight)
- Blood routine, blood biochemistry (Hepatic and renal function, blood glucose (fasting), blood lipids, myocardial enzyme, electrolytes and homocysteine), urine routine, coagulation function and ECG examination
- NIHSS score
- mRS score

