### 7.2. Safety measures

#### 7.2.1. Safety evaluation indexes

- Vital signs and physical examination, including heart rate, blood pressure, body temperature and respiratory rate. Physical examination is evaluated by organ and system;
- Laboratory test, including blood routine, urine routine (qualitative or quantitative), blood biochemistry (including hepatic and renal function, blood glucose, blood lipids, myocardial enzyme, electrolyte), coagulation function, electrocardiogram, pregnancy test (women of childbearing age). See Table 7.2- 1 for detailed test items

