## **4 Statistical Analysis**

### **4.1 General Principles**

All statistical analyses for this study will be performed using the statistical analysis software SAS version 9.4 or higher. All data collected in Case Report Form (CRF) will be statistically calculated by treatment groups. For continuous variables, the number of subjects with non-missing data, mean, standard deviation, median, minimum, and maximum were calculated and listed. The number of decimal places for the minimum and maximum values will be

consistent with that recorded in the database. Means, medians, and standard deviations will be rounded to one more decimal place than the raw data recorded in the database. For discrete variables, frequencies and percentages were calculated and presented. Percentages will be presented to one decimal place.

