  - Concomitant medication end date is only missing for Day: Impute as last day of month.
  - Date of first dose appointment: Date of start of treatment period

Dates in the data listings were listed as completed on the eCRF.

- 3) Definition of baseline: The last non-missing data before the first dose is baseline. If a subject took trial medication but did not have a date of first dose, the last non-missing data prior to the date of enrollment was taken as baseline.
- 4) Change from baseline was defined as: test value at post-treatment follow-up – baseline test value.

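### SAP 4.4.4 compares vital signs between arms only by a count of patients elevated to Day 14, with no threshold, no decreases and no size of change

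*Combined protocol and SAP*

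**What the plan says.** Protocol 2.2.3 lists as a safety outcome "Changes in vital signs and laboratory data in each group before and after treatment". SAP 2.3 repeats it as "changes in vital signs and laboratory data before and after treatment". Neither gives a direction.

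Protocol 7.2.1 defines the measurements: "Vital signs and physical examination, including heart rate, blood pressure, body temperature and respiratory rate". The flow chart and protocol 6.1 to 6.3 schedule them at screening and at Days 7, 14, 30 and 90.

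For the analysis, SAP 4.4.4 states that "the number and percentage of subjects with elevated in vital signs from baseline to day 14 after randomization will be described", and compares the arms with Fisher's exact test. It does not define elevation or name the parameters. Protocol 8.5 gives no vital-sign method. SAP 4.2.3 summarises blood pressure, but among the baseline characteristics.

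Two general rules also apply. SAP 4.1 says that "All data collected in Case Report Form (CRF) will be statistically calculated by treatment groups" and adds: "For continuous variables, the number of subjects with non-missing data, mean, standard deviation, median, minimum, and maximum were calculated and listed". SAP 4.1.3 gives a signed definition: "Change from baseline was defined as: test value at post-treatment follow-up" minus the baseline value.

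**The concern.** The outcome is undirected change, but the one comparison written for it looks in one direction and stops at Day 14. A patient whose pressure or heart rate drops is counted together with a patient who does not change. The count also discards how large a change was. Because elevation has no stated cut-off, the cut-off has to be chosen later, and that choice affects the result.

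Both directions are relevant here. Protocol 1.3 lists shock among the serious adverse reactions in the Japanese label for edaravone injection. Protocol 1.2.3.2 reports a slight, transient, dose-dependent rise in blood pressure in dogs. That is modest support, because the same sentence includes the control solvent and the pressure was normal again within 60 minutes.

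What is at stake is how informative the safety report is. No efficacy conclusion depends on this.

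**Working it through.** **1. The plan's own figures.** SAP 4.4.4 contains no figure to reproduce. The arm size used below comes from SAP 2.5 (50% v 40%, two-sided 0.05, power 80%, 15% dropout), and it reproduces:

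- n = [1.96 × √(2 × 0.45 × 0.55) + 0.8416 × √(0.25 + 0.24)]² / 0.10² = 387.3, so 388 per arm.
- 388 / 0.85 = 456.5, so 457 per arm and 914 in total.

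**2. The texts side by side.**

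| Data | Change from baseline specified? | By visit? | Between-arm comparison |
|---|---|---|---|
| NIHSS (SAP 4.3.2) | Yes | Observed values and change at each visit | Day 14 mean difference with 95% CI |
| Blood routine and biochemistry (SAP 4.4.4) | Yes, changes after treatment; protocol 8.5 adds a before-after mean comparison | Not stated | Fisher's test on clinically significant abnormality |
| Vital signs (SAP 4.4.4) | No | To Day 14 only | Fisher's test on the undefined elevated count |

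Where the authors wanted change scores, they wrote them in, and for vital signs they did not. Day 7 may fall within the period to Day 14. Days 30 and 90 do not.

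**3. Illustration of the information lost.** The documents give no SD or effect size for vital signs, so every input here is an assumption except n = 457 and alpha = 0.05. Assume normal change scores with SD 20 mmHg in both arms, control mean change 0, active mean change +3 mmHg, and elevation read as any rise above zero.

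- Mean change: SE = 20 × √(2/457) = 1.323; z = 3 / 1.323 = 2.27; power = Φ(2.27 − 1.96) = 62%.
- Count: P(rise) = 0.500 v Φ(3/20) = 0.560; SE = √[(0.500 × 0.500 + 0.560 × 0.440)/457] = 0.0330; z = 0.0596 / 0.0330 = 1.81; power = Φ(1.81 − 1.96) = 44%.

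Range over the assumptions:

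- A 5 mmHg difference, same SD: 97% by means v 85% by count.
- 388 per arm in place of 457, 3 mmHg: z = 2.09 (55%) v 1.67 (38%).
- A 4 mmHg difference, 457 per arm, SD 15 / 20 / 25: 98 / 86 / 68% by means, against 84–89 / 60–64 / about 46% by simulated Fisher's exact tests (control mean change −10 to 0 mmHg).
- A cut at a rise of 30 mmHg in place of zero (SD 20, 3 mmHg difference): 6.7% v 8.9% beyond the cut; SE = √[(0.067 × 0.933 + 0.089 × 0.911)/457] = 0.0177; z = 1.23; power about 23%.

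A split at zero keeps about 2/π = 64% of the information when mean change is near zero.

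**4. A case that the any-rise count misses entirely.** Suppose the drug only widened the spread, from SD 15 to SD 25 mmHg with mean change 0. The share with any rise stays at 50% in both arms. Falls of 30 mmHg or more go from Φ(−30/15) = 2.3% to Φ(−30/25) = 11.5%.

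**The case against.** The strongest reply is that SAP 4.4.4 does not stand alone. SAP 4.1 already promises means, SDs, minima and maxima by arm for everything in the CRF, so it would be wrong to infer that vital signs are summarised only as a count or that falls are never reported. Protocol 7.3.1 makes clinically significant abnormal vital signs adverse events. These are collected to Day 90 and compared with 95% CIs under SAP 4.4.2. All of this stands. But SAP 4.1 does not require change from baseline, summaries by visit or a between-arm estimate, and adverse events capture only what an investigator judged significant.

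A reader might also infer that any rise counts, so that about half of each arm would be elevated through noise alone. The SAP does not say this. Elevation could equally mean above a normal range or a clinical limit. Even with a cut at zero, half follows only if mean change is zero: with a control mean change of −10 and SD 20 the share is 31%. The power figures therefore illustrate one reading.

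A uniform fall would also leave a trace in an any-rise count. With a 5 mmHg fall and SD 20, the elevated share would be 1 − Φ(0.25) = 40% v 50%. But that would read as fewer rises. It would not show how many patients fell, or how far.

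Finally, Day 14 is a reasonable main time point. Dosing lasts 14 days, and mean half-lives in protocol 1.2.3.5 are at most 7.9 hours. That supports giving Day 14 priority. It does not justify leaving measurements taken at Days 30 and 90 without a stated analysis.

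**Conclusion.** The point holds as a limited weakness in safety reporting. The only vital-sign-specific post-baseline analysis and comparison uses an undefined elevated count to Day 14. It does not compare decreases or size of change, and it omits Days 30 and 90, although the stated outcome is undirected change. The general summaries and adverse-event tables reduce the gap without closing it.

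Its size cannot be fixed from the documents. In the illustration, the loss is 18 points of power (62% to 44%) for a 3 mmHg difference. This rests on an assumed SD of 20 mmHg, 457 analysed per arm, no mean change in controls and a cut at zero. The trial was not powered for vital signs, and the primary analysis and sample size are untouched.

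**What to change.** Replace the vital-sign sentence in SAP 4.4.4 with text to this effect:

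- For heart rate, systolic and diastolic blood pressure, body temperature and respiratory rate, summarise change from baseline (as defined in SAP 4.1.3) by arm at Days 7, 14, 30 and 90. Give the between-arm mean difference with its 95% CI, and name Day 14, the end of treatment, as the main time point.
- For each parameter, report the number and percentage of patients beyond a pre-specified threshold for increase and, separately, for decrease. Keep Fisher's exact test for these counts. The trial's clinicians should set the thresholds and write them into the SAP.

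The data are already collected, so the cost is a few extra tables. The third IDMC meeting agreed to lock the database. Any threshold or table added after unblinding should be labelled as such in the report.
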